
#### 2.3.2. Secondary Explanatory Variable

Satisfaction and usefulness: The acceptance and usefulness of telemedicine applications is a prerequisite for identifying the potential clinical benefits of this technology. It is therefore important to complement this research with tools that examine patient satisfaction and perception [29]. An adaptation of the Telemedicine Satisfaction and Usefulness Questionnaire (TSUQ), whose psychometric analysis supports construct validity and internal consistency reliability, and which is available in English and Spanish, will be used [29]. The instrument used showed high reliability (Cronbach’s alpha 0.8) and evidence of validity with respect to perception in telemedicine [30]. It includes 17 questions that are assessed with a 5-point Likert subjective scale (1 totally disagree and 5 completely agree). The individual obtains scores from 17 to 85. The higher the score, the better the perception of the telerehabilitation intervention. Therefore each of the scores of the 17 variables indicated and finally the total score of the Test will be analyzed [29,30].

Analysis of the cost-effectiveness: To assess the cost-effectiveness of the telerehabilitation intervention, the international guidelines for conducting cost analyses in randomized clinical trials will be followed [31]. Such an economic analysis is based on the health sector perspective, which means that only costs corresponding to health interventions will be considered, and not related costs to the patient. Therefore, only costs related to the provision of health services will be taken into account [32].

Costs are divided into two categories of variables: firstly, costs related to clinical aspects (direct costs) and secondly, costs related to the use of the technology (indirect costs).

Direct costs: Numerical variable calculated on the basis of the number of hours of intervention and the cost of the physiotherapist according to the hourly wage in the health system in the centers where the research is carried out. It will be calculated based on the recording of the number of sessions in both groups.

Indirect costs: Numerical variable calculated based on the cost of using the technology for the telerehabilitation platform.

Adherence and safety: Participants will be advised to report and record barriers of use and any adverse event during the study. Number of sessions are automatically registered by the CTR tool.

The Charlson Comorbidity Index (CCI) will be included in the demographic, anamnesis and medical history data [33]. CCI is a system for evaluating life expectancy at ten years, depending on the age at which it is evaluated and the subject’s comorbidities. 

We will try to ensure that the sample data are similar at baseline and there are no significant differences in demographic, medical and other outcomes. The homogeneity of the sample will be analyzed and normality tests will be performed. An outline of the primary (4 dimensions) and secondary outcomes (3 dimensions) is shown at Table 2:

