Despite the fact that CTR has been shown to be as effective as CR in the hospital and home environment in terms of exercise capacity and quality of life, to be cost-effective and to improve patient satisfaction and adherence, its implementation in the public and private healthcare environment is still scarce and limited [4,16,17]. Considering the current health era and the large number of patients with cardiovascular diseases, it is advisable to carry out feasibility, safety, and effectiveness studies in the implementation of cardiac telerehabilitation programs both in the hospital environment and in other areas of care.

The aim of this research was to evaluate the efficacy, feasibility, and adherence of a telerehabilitation program in low-risk cardiac patients in the hospital of Melilla (Spain).

The secondary aims of this trial were to investigate patient satisfaction, to identify barriers of implementation and adverse events, and to assess cost-effectiveness from a health system perspective (costs of health interventions).

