### 2.2. Intervention

Participants are assigned to the cardiac telerehabilitation group to receive an initial assessment. The CTR group receives a personalized 8-week exercise program through a mHealth application that allows health professionals to generate videos, images, and parameters of each exercise, as well as send them by email, instant messaging, and follow up on patients. In this study, we use the Physiotec exercise prescription app as it allows us to create personalized CTR programs according to particular clinical case and follow their progress. The CTR program describes the exercises to be performed, the number of repetitions according to the level of training and the criteria for progression. The CTR program includes aerobic exercise at 60–85% of the maximum heart rate (HR) reached in the ergometry test. As patients are taking β-blocker drugs, they will never reach their maximum HR. Patients will be instructed in the use of the Modified Borg Scale to assess their level of fatigue while performing the CTR program. Exercises customized to each participant should be performed between values 4–6 on this scale (out of a maximum of 10).

The type of exercise can be continuous or intervallic (load or HR controlled):

Continuous Exercise: After an initial warm-up period of 5–10 min, the patient is brought into a phase where he or she remains at a HR or resistance previously determined by the intervention team.

Interval Exercise: After an initial warm-up period, an exercise is started which alternates load peaks with lower intensity ones.

All patient training sessions should end with a return to the initial baseline situation (relaxation phase) of similar duration to the warm-up phase 5–10 min.

Typical CTR training session: -Control of basal constants (by the patient): HR, blood pressure, weight, blood sugar…-Permanent monitoring during the whole CTR session (patient must understand and follow the modified Borg scale as well as to use activity bracelets, pulse meters, or other monitoring instruments)-Exercise session:
∘Initial warm-up: 5–10 min (follow-up the video exercises provided through the CTR tool).∘Aerobic training: 35–45 min (follow up the video exercises provided through the CTR tool)∘Return to calm, relaxation-cooling: 5–10 min (follow up of the video exercises provided through the CTR tool)∘Recording of incidents and patient feedback in the CTR tool. Patient/physiotherapist feedback

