Patients are initially supervised by the research team who will conduct 1-to-1 training sessions to ensure proper execution of the exercises and encourage patient adherence. Patients are instructed to perform self-training by following the video exercises through the CTR program. At the beginning of the study, advice is given on general care, in physical activity and issues concerning drug intake.

Patients are advised to refrain from any other specific training during the intervention period. Any deviations from the adherence and practice of the CTR program are recorded daily, noting any adverse incidents.

The TR group receives a personalized program for 8 weeks, including at least one session per day and is done through a web and mobile application. The telerehabilitation application allows health professionals to create personalized exercise programs, hold video conferences with patients, generate videos, images and parameters of each exercise, as well as send them by email and follow up patients through the mobile application.

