### 2.5. Statistical Analysis

This research is a single center prospective controlled trial pre/post design. The results of the trial research will be presented as a summary of the outcome measures, together with the estimated effect size and precision. Statistical analysis will be performed according to the intention-to-treat principle. Patient characteristics will be summarized using frequencies and percentages for categorical factors, and using means and standard deviations for continuous measures in order to have as much information as possible available for exploration and analysis. The effect sizes will be calculated using Cohen’s d, so that the results can be compared to other studies. The outcome measures will be compared before and after the completion of the 8-week CTR program. All statistical analyses will be conducted using SPSS software. Statistical significance was set at *p* < 0.05.

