Future lines of research would involve the development of clinical trials with a large sample size; a qualitative approach to attend focus groups to explore their thoughts and concerns about the intervention. Themes will be constructed from the data to give insight into the experiences of the different participant groups. As participation is important for rehabilitation departments, it is essential to include the participants’ perspective in the evaluation of the treatment. Finally, the opportunity to develop a multicenter randomized clinical trial with comparison groups performing in-hospital or home-based rehabilitation programs has the aim of identifying the most appropriate intervention.

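### The costing rule refers to two groups in a one-group trial, so no incremental cost-effectiveness ratio can be formed, and it does not say which sessions generate physiotherapist hours

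*Protocol article*

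**What the plan says.** The Introduction lists as a secondary aim "to assess cost-effectiveness from a health system perspective (costs of health interventions"). Cost-effectiveness is also named in the Abstract, is an outcome in Table 2, and is one of the results on which the Conclusions rest the case for CTR.

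Section 2.3.2 defines direct cost as a "Numerical variable calculated on the basis of the number of hours of intervention and the cost of the physiotherapist according to the hourly wage" and adds: "It will be calculated based on the recording of the number of sessions in both groups". Indirect cost is the cost of using the platform. The section says it follows guidelines for cost analyses in randomized trials.

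On design, section 2.2 says "Participants are assigned to the cardiac telerehabilitation group to receive an initial assessment". Section 2.5 says "This research is a single center prospective controlled trial pre/post design" and "The outcome measures will be compared before and after the completion of the 8-week CTR program". The Discussion places "the opportunity to develop a multicenter randomized clinical trial with comparison groups" among future work.

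On delivery, section 2.2 says "Patients are instructed to perform self-training by following the video exercises through the CTR program", after initial 1-to-1 training. Section 2.4 (Stage 3) describes supervision by the physiotherapy department and CTR staff over the 8 weeks, daily follow-up and programme updates.

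**The concern.** There are two separate problems.

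**No comparator.** Cost-effectiveness is a statement about extra cost and extra effect relative to an alternative. The costing rule presupposes a second group, but the article defines no second group and no sessions, costs or effects for one. If the aim stays as worded, a single-arm pilot could report a cost-effectiveness conclusion that its design cannot support. Pre-post change does not stand in for an incremental effect. Section 2 leaves medication to the treating physician while the programme runs, so a change over 8 weeks is not attributable to CTR alone.

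**Undefined staff hours.** The rule converts a session count into hours paid at a physiotherapist's wage. Much of the exercise is self-training from videos at home. The staff work described lies in 1-to-1 training, daily follow-up and programme updates. The rule does not say which of these counts as a session for costing. If self-training sessions were counted, better adherence would raise the computed staff cost whether or not staff time rose. That would hide the feature that economically distinguishes telerehabilitation from supervised sessions.

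**Working it through.** The article states no cost, wage, hours total or ratio, so there is no figure of its own to reproduce.

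**Step 1: number of groups.**

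| Place | What it implies |
|---|---|
| 2.3.2, direct costs | Two groups |
| 2.2 | One group, CTR; no other allocation described |
| 2.4, Stages 1 to 4 | One pathway, leading to the CTR programme |
| 2.5 | Within-patient comparison, before and after |
| 4, Discussion | Comparison groups in a future trial |

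An incremental ratio is (cost under CTR − cost under alternative) / (effect under CTR − effect under alternative). Both alternative terms are missing, so it cannot be formed. The average ratio, CTR cost / mean pre-post change, needs only the one group and can be formed.

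**Step 2: hours if every planned session is charged at full length.** Inputs are from section 2.2: at least one session a day for 8 weeks; warm-up 5–10 min, aerobic part 35–45 min, cool-down 5–10 min.

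- Sessions: 8 × 7 × 1 = 56 per patient, as a minimum
- Session length: 5 + 35 + 5 = 45 min to 10 + 45 + 10 = 65 min
- Hours per patient: 56 × 45/60 = 42.0 to 56 × 65/60 = 60.7
- For 30 patients: 30 × 42.0 = 1,260 h to 30 × 60.7 = about 1,820 h

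**Step 3: hours if only staff time is charged.** The article gives no follow-up minutes. It also does not fix the number of 1-to-1 sessions: section 2.2 uses the plural, section 2.4 describes one initial session. Both are therefore assumptions. Let *k* be the number of full-length 1-to-1 sessions and *f* the follow-up minutes on each remaining day. For session length *L*, staff hours = [*k* × *L* + (56 − *k*) × *f*] / 60. The ratio is Step 2 hours divided by these.

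| *k* | *f* (min) | Staff hours per patient (*L* = 45 to 65) | Ratio (*L* = 45 to 65) |
|---|---|---|---|
| 1 | 0 | 0.75–1.08 | 56 |
| 1 | 5 | 5.3–5.7 | 7.9–10.7 |
| 1 | 10 | 9.9–10.3 | 4.2–5.9 |
| 1 | 15 | 14.5–14.8 | 2.9–4.1 |
| 5 | 15 | 16.5–18.2 | 2.5–3.3 |
| 1 | 30 | 28.3–28.6 | 1.5–2.1 |
| 1 | 45 | 42.0–42.3 | 1.0–1.4 |

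For example, *k* = 1, *f* = 5, *L* = 65 gives (65 + 55 × 5)/60 = 5.7 h, and 60.7/5.7 = 10.7 before rounding.

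Two limits apply. Time spent building and updating programmes is left out, and including it would lower every ratio. The 56 sessions are those planned, whereas Table 2 counts sessions completed, so actual hours would be lower with imperfect adherence.

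**The case against.** Several points on the other side are sound.

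- **The hours may already mean staff hours.** The definition can be read as physiotherapist hours. Nowhere does the article say that a home session is charged at full length.
- **The costed sessions may not be the app's sessions.** Automatic registration appears in the adherence and safety paragraph of section 2.3.2, not in the costing paragraph. Table 2 types only adherence and safety as an automated app record. Section 2.4 also uses the word session for staff contact.
- **Staff are involved throughout.** Section 2.4 describes supervision across the 8 weeks, and section 2.2 says the application allows video conferences.
- **This is a condensed article on a 30-patient pilot.** How staff minutes are logged may properly sit in a fuller document.

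These points stand against two stronger readings. A reader might infer that direct cost is certainly overstated, perhaps 4- to 11-fold. That band follows only from assuming one 1-to-1 session and 5 to 10 minutes of follow-up a day, and the article supports neither figure. A reader might also infer that no ratio of any kind can be computed, but the average ratio can.

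The points do not remove the contradiction about groups. The label *controlled* might suggest an undescribed control arm, but section 2.5 pairs it with a pre/post comparison and no other arm appears in the text. A fuller document could add costing detail, but the article's statement would still conflict with its own design.

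**Conclusion.** The point holds in two parts of different strength.

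The first is firm and rests on the article's text alone. The costing rule refers to a second group that the design lacks, so no incremental cost-effectiveness ratio can be formed. A computable average cost per unit of change would not answer the aim.

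The second is an ambiguity with possible consequences. The rule does not separate physiotherapist time from self-training sessions. Charging all planned sessions at full length gives 42 to 61 wage hours per patient. Whether that would happen is not stated, and the resulting overstatement cannot be determined: it runs from about none, if follow-up lasts nearly as long as a session, to 56-fold, with one supervised session and no follow-up time. It should be described as possible, not as shown.

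The correction should be made because it changes what the trial may conclude on cost. It concerns a secondary aim and touches no primary outcome, so it is not of the highest severity.

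**What to change.** 1. In section 2.3.2, delete the reference to both groups.
2. In the Abstract, section 1, section 2.3.2, Table 2 and section 5, relabel the aim and outcome as a descriptive cost of delivering CTR per patient, and draw no cost-effectiveness conclusion. Keeping the present aim would require a defined comparator with its own costs and effects, which the Discussion leaves to a later trial.
3. Define direct cost as recorded physiotherapist time (1-to-1 sessions, daily follow-up, programme updates) multiplied by the hourly wage. Use app-logged sessions for adherence only.
4. Reconcile sections 2.2 and 2.4 on whether there is one 1-to-1 session or several, since this enters the staff time.

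The cost is a few wording changes and a record of staff time. The downside is that the cost-effectiveness claim is dropped. The descriptive cost remains useful for planning the larger trial.

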#### 2.3.1. Main Explanatory Variable

-Biochemical outcomes: obtained by blood analysis performed at the Hospital of Melilla including the following measures: red blood cell levels, glucose, creatine kinase (CK), triglycerides, cholesterol, high-density lipoprotein cholesterol (HDL-C), low-density cholesterol (LDL-C), and glycosylated hemoglobin (HbA1c).-Cardiac function: obtained by performing an ergometry test at the Hospital of Melilla, including the following measurements: metabolic equivalent (MET), resting heart rate (HRrest), maximum heart rate (HRmax), and final heart rate (HRfinal), rating of perception of exertion scale (RPE), systolic blood pressure (SBP), diastolic blood pressure (DBP).-Quality of life: obtained through the completion of self-reported questionnaires with the advice of the research team. The assessment of health-related quality of life will be assessed by the following two questionnaires: SF-12 and EuroQoL-5d. The SF-12 questionnaire is the short version of the SF-36, containing twelve questions from the SF-36. [21]. The SF-12 is an appropriate instrument of choice and is a practical alternative for measuring the general health status of the population [22]. The SF-12 questionnaire assesses eight dimensions of health-related quality of life: physical function, physical role, bodily pain, general health, vitality, social function, emotional role, and mental health [21]. Two sum scores are also obtained for the physical health component and the mental health component of the person. Thus, the sum index of the physical and mental component corresponds to the overall idea of general health. The EuroQoL-5D Questionnaire (EQ-5D) contains a descriptive system of one’s health status measured in five dimensions (mobility, self-care, activities of daily living, pain, and anxiety/depression) [23]. The EQ-5D has a visual analog scale (VAS) that assesses health status “on the present day” with scores ranging from 0 (worst imaginable health status) to 100 (best imaginable health status). The EQ-5D questionnaire provides information on the level of the problem (no problem, somewhat/moderate problem or severe problem) [24]. It has been shown to be a tool with an acceptable validity, with an estimated mean of 0.87 [25].-Functional capacity: For the assessment of functional capacity we will use the Duke Activity Status Index (DASI). It is an assessment tool used to evaluate the functional capacity of patients with cardiovascular disease, such as coronary artery disease, myocardial infarction, and heart failure. It is a validated instrument and its Spanish version is available [26,27]. The original version include 12 questions on aspects of physical function related to activities of daily living. It allows a calculation of functional capacity reporting results in ml of O2/kg/minute with good correlation with peak VO2, and in turn can be compared with the METs [28].

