## 3. Results

Enrollment began in February 2021. First study results will be reported in the middle of 2021. Recruitment is currently underway. The recruitment goal is 30 cardiac rehabilitation patients. Data collection is anticipated to be complete by July 2021.

If the results confirm beneficial effects in biochemical, cardiac function, quality of live, and functional capacity, the effectiveness of the intervention will be proven in patients with heart failure. The successful delivery of the intervention, the absence of significant adverse effects, and the user satisfaction will demonstrate the feasibility of these interventions in cardiac patients.

The results of this study will determine if a larger-scale intervention is feasible. Further, this pilot study will be the first to examine the effect of CTR intervention on patients in a cardiac rehabilitation setting in Melilla (Spain). The results of this study will provide differences compared to previous research: first of all, its implementation in the autonomous city of Melilla (located on the African continent with particular demographic characteristics); secondly the use of the innovative CTR platform based on the App Physiotec; thirdly, the collection of outcomes that combine clinical, self-reported and economic data and lastly, automated treatment adherence registry.

This study will add more evidence in support of the use of CTR program as an effective tool in new cardiac rehabilitation programs.

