## Figures and Tables

**Figure 1 ijerph-18-04038-f001:**
[figure not shown]
Study design. Abbreviations CVD, cardiovascular disease; CTR, cardio-telerehabilitation.

**Table 1 ijerph-18-04038-t001:** Inclusion and exclusion criteria.

Inclusions Criteria	Exclusions Criteria
Adult over 18 Years old	Cognitive ability not suitable for the use of technologic tools.
Diagnosis: Ischemic heart disease in New York Heart Association (NYHA) functional class I-II with preserved global systolic function or in intermediate range (LVEF > 40%) after revascularized acute coronary syndrome.	
Lives in Melilla during the research period.	Absolute or relative contraindications to exercise testing
To have mobile technology with an internet connection at home (including one of the following devices: desktop personal computer, laptop, tablet, or smartphone)	
Ability and knowledge to access email or instant messaging	

Abbreviations LVEF, Left ventricular ejection Fraction.

**Table 2 ijerph-18-04038-t002:** Primary and secondary outcomes.

	Definition	Type
Primary Outcomes		
Biochemical	Hematies Level, Glucose, Creatine Kinase (CK), Triglycerides, Total Cholesterol, High Density Lipoprotein Cholesterol (HDL-C), Low Density Lipoprotein Cholesterol (LDL-C), Glycated Hemoglobin (HbA1c)	Clinical
Cardiac Function	Metabolic Equivalent (MET), Resting Heart Rate (RHR), Maximum Heart Rate (HRmax), Final Heart Rate (FHR), Rating Scale for Perceived Exertion (RPE), Systolic Blood Pressure (SBP), Diastolic Blood Pressure (DBP)	Clinical
Quality of Life	SF-12, EQ-5D	Self-Reported
Functional Capacity	Duke Activity Status Index (DASI)	Self-Reported
Secondary Outcomes		
Feasibility, Satisfaction and Usefulness	Telemedicine Satisfaction and usefulness Questionaire (TSUQ)	Self-Reported
Cost-Effectiveness	Direct Costs/Indirect Costs	€/Self-Reported
Adherence and Safety	Nº of sessions completed and adverse events record	Automatized App record

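### At least 18 measures are labelled primary with none leading, and the sentence declaring effectiveness proven does not say which or how many must improve, so the false-positive rate is undefined

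*Protocol article*

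**What the plan says.** Section 2.3.2 introduces Table 2 with "An outline of the primary (4 dimensions) and secondary outcomes (3 dimensions) is shown". The contents of the four primary dimensions are given in Section 2.3.1 and repeated in Table 2:

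- Biochemical, eight measures: "red blood cell levels, glucose, creatine kinase (CK), triglycerides, cholesterol, high-density lipoprotein cholesterol (HDL-C), low-density cholesterol (LDL-C), and glycosylated hemoglobin (HbA1c".
- Cardiac function, seven measures: "metabolic equivalent (MET), resting heart rate (HRrest), maximum heart rate (HRmax), and final heart rate (HRfinal), rating of perception of exertion scale (RPE", followed by systolic and diastolic blood pressure.
- Quality of life: SF-12 and EQ-5D.
- Functional capacity: the Duke Activity Status Index (DASI) alone.

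Neither place ranks these measures or names a leading one.

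Section 2.5 states one comparison for all of them: "The outcome measures will be compared before and after the completion of the 8-week CTR program". It gives one threshold: "Statistical significance was set at *p* < 0.05". It also promises effect sizes with their precision.

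Section 3 supplies the decision sentence. It opens with "If the results confirm beneficial effects in biochemical, cardiac function, quality of live, and functional capacity" and concludes that effectiveness will then have been proven in patients with heart failure.

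**The concern.** A primary outcome fixes, before results are seen, what the trial's efficacy claim will rest on. Here that role is shared by at least 18 measures. The claim is triggered by benefit in a dimension, but a dimension such as the biochemical one contains eight measures, and the article does not say whether one, most or all of them must move. Nor does it say what follows if only some dimensions improve.

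Without that rule, a reader cannot say what false-positive rate the claim carries. A single improved laboratory value or ergometry reading could be presented as the efficacy result, and so could a stricter combination, both consistently with the text. The issue matters more because Section 3 speaks of proof, in a study of 30 patients that the article itself calls a pilot.

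**Working it through.** **Inputs.** The measures per dimension come from Section 2.3.1 and Table 2. The threshold of 0.05 comes from Section 2.5. Sidedness is not stated. I take tests as two-sided, so each has a 0.025 chance of a false result in the favourable direction. The article gives no family-wise error rate and no power calculation, so there is no plan figure to reproduce beyond the 0.05 itself.

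**Count.** 8 biochemical + 7 ergometry + 2 questionnaires + 1 DASI = 18. This takes SF-12 and EQ-5D as one outcome each, so it is the minimum.

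**Reading A: any one measure may carry the claim.** With no true change and independent measures:

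- At least one significant result in either direction: 1 − 0.95^18 = 0.603.
- At least one significant favourable result: 1 − 0.975^18 = 0.366.
- Expected number of false significant results: 18 × 0.05 = 0.9.

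The measures are unlikely to be independent; total cholesterol and LDL-C, or the heart-rate measures, are obvious examples. The article gives no correlations, so a common correlation is assumed and the probabilities are found by simulating equicorrelated normal test statistics.

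**Reading B: at least one favourable result in every dimension.** Under independence this is the product of the four dimension probabilities:

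- Biochemical: 1 − 0.975^8 = 0.183
- Cardiac function: 1 − 0.975^7 = 0.162
- Quality of life: 1 − 0.975^2 = 0.049
- Functional capacity: 0.025

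Product: 0.183 × 0.162 × 0.049 × 0.025 ≈ 0.00004. Correlation raises it, but it can never exceed 0.025, because DASI alone must succeed.

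| Assumed common correlation | A: any significant result | A: any favourable result | B: favourable in all four dimensions |
|---|---|---|---|
| 0 | 60% | 37% | <0.01% |
| 0.3 | 51% | 26% | 0.2% |
| 0.5 | 40% | 20% | 0.6% |
| 0.7 | 28% | 14% | 1.1% |

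**After a fix.** One named primary: 0.05. One named measure per dimension, any of which may win: 1 − 0.95^4 = 0.185 unadjusted, and 1 − (1 − 0.0125)^4 = 0.049 with Bonferroni.

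**The case against.** The strongest reply is that Section 3 joins the four dimensions with *and*. Read literally, all four must improve, and chance success is then about 1% or less. This stands as far as it goes, and it is why an error rate above 5% cannot be asserted without condition. It does not close the matter. The sentence still does not define benefit within a dimension or say what is concluded when only some dimensions improve.

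A second reply is that a multiplicity method, the handling of subscales and the direction of benefit for each laboratory value could sit in an analysis plan or full protocol that is not shown. That also stands, and no weight is placed on their absence here. The point rests on what the article does fix: the primary labels, one threshold and the sentence claiming proof.

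A third reply is that this is a pilot. Section 2.1 leaves adequate power to a larger trial, and Section 2.5 promises estimates with precision. An exploratory reading would be reasonable, but it conflicts with the language of proof in Section 3.

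Two stronger readings are tempting. A reader might infer that a chance benefit is more likely than not. The 60% figure does not show this: it counts results in either direction, harm included, and assumes independence. For favourable results among 18 measures the figure is 37%, or 20-26% at correlations of 0.3-0.5. A reader might also count 32 primaries by adding eight SF-12 domains, two summary scores, five EQ-5D dimensions and the visual analogue scale (8 + 7 + 16 + 1). That would give 1 − 0.95^32 = 81% for any significant result, but Section 2.3.1 only describes these instruments. It does not say that each subscale is tested.

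**Conclusion.** The point holds in a conditional form. The article labels at least 18 measures as primary with none leading, applies one threshold to the pre/post comparisons, and claims proof of effectiveness under a rule it does not define.

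Under the loosest reading, a false favourable result has a probability of 37% if measures are independent and 20-26% at correlations of 0.3-0.5. A single two-sided test at 0.05 allows 2.5% in that direction, so even the 20% figure is eight times as large. Under the strictest reading, the probability is about 1% or less. The width of that range is the finding: the text does not determine where in it the trial lies.

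The figures assume no true change in any measure, two-sided tests, 18 outcomes and, where stated, a common correlation chosen for illustration.

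**What to change.** Before any post-programme (T1) data are examined:

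- Name one primary efficacy outcome that is already collected, with its time point, and test only that at 0.05. Change in METs at ergometry is one suitable example; another single measure would serve equally well for this purpose.
- Move the other primary measures in Table 2 to secondary or exploratory, and report each as mean change with a 95% confidence interval.
- Rewrite the Section 3 sentence to refer to the named outcome, and drop the claim of proof. Naming one primary does not by itself justify that claim, because the comparison in Section 2.5 is before against after, and Section 2.2 describes assignment to the telerehabilitation group only.

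An acceptable alternative is an explicit decision rule over the four dimensions with one named measure each. If all four must succeed, each can be tested at 0.05. If any may succeed, 0.05 / 4 = 0.0125 each keeps the overall rate at about 0.049.

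The cost is a short amendment to Table 2, Section 2.5 and Section 3, with no new data collection. The downside is that the remaining measures can no longer carry a formal efficacy claim.
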